### Case Report Forms

For each subject consented, a CRF will be completed by an authorized study staff member whose training for this function is documented according to study procedures. CRF should be completed on the day of the subject visit to enable the sponsor to perform central monitoring of safety data. Prior to database lock (or any interim time points as described in the clinical data management plan), study staff will use his/her log in credentials to confirm that the forms have been reviewed, and that the entries accurately reflect the information in the source documents. The CRF capture the data required per the protocol schedule of events and procedures.

### Investigational Medicinal Product Accountability and Return

Used (empty or partially empty) and unused study drug supplies will be destroyed on site according to appropriate standard operating procedure (SOP). A copy of the site’s approved SOP will be obtained for central files.

If study drug is destroyed on site, the investigator must maintain accurate records for all study drug destroyed. Records must show the identification and quantity of each unit destroyed, the method of destruction, and the person who disposed of the study drug. Upon study completion, copies of the study drug accountability records must be filed at the site. Another copy will be returned to Gilead.

The study monitor will review study drug supplies and associated records at periodic intervals.

### Inspections

The investigator will make available all source documents and other records for this trial to Gilead’s appointed study monitors, to IRBs, or to regulatory authority or health authority inspectors.

### Protocol Compliance

The investigator is responsible for ensuring the study is conducted in accordance with the procedures and evaluations described in this protocol.

## Gilead Responsibilities

### Protocol Modifications

Protocol modifications, except those intended to reduce immediate risk to study subjects, may be made by the investigator. The investigator must submit all protocol modifications to the IRB in accordance with local requirements and receive documented IRB approval before modifications can be implemented. The investigator will also notify Gilead.

### Study Report and Publications

No such communication, presentation, or publication will include Gilead’s confidential information (see Section 10.1.4).

The investigator will comply with Gilead’s request to delete references to its confidential information (other than the study results) in any paper or presentation.

## Joint Investigator/Gilead Responsibilities

### Payment Reporting

Investigators and their study staff may be asked to provide services performed under this protocol, e.g. attendance at Investigator's Meetings. If required under the applicable statutory and regulatory requirements, Gilead will capture and disclose to Federal and State agencies any expenses paid or reimbursed for such services, including any clinical trial payments, meal, travel expenses or reimbursements, consulting fees, and any other transfer of value.

### Access to Information for Monitoring

In accordance with regulations and guidelines, the study monitor must have direct access to the investigator’s source documentation in order to verify the accuracy of the data recorded in the CRF.

### Access to Information for Auditing or Inspections

Representatives of regulatory authorities or of Gilead may conduct inspections or audits of the clinical study. The investigator agrees to provide to representatives of a regulatory agency or Gilead access to records, facilities, and personnel for the effective conduct of any inspection or audit.

### Study Discontinuation

The investigator reserves the right to terminate the study at any time. Should this be necessary, both the investigator and Gilead will arrange discontinuation procedures and notify the appropriate regulatory authority(ies) and IRB. In terminating the study, Gilead and the investigator will assure that adequate consideration is given to the protection of the subjects’ interests.

**APPENDICES**

Appendix 1. Study Procedures Table

Appendix 2. Estimating Severity Grade for Parameters Not Identified in the Grading Table

Appendix 1. Study Procedures Table

Screening, Weekly Visits (mDOT and unobserved dosing arms), and Post-Treatment Visits

| Clinical Assessments | | Screening visits | Enrollment | Visit identified by study week | | | | | | | | | | Post-treatment visits | | | |
| --- | --- | --- | --- | --- | --- | --- | --- | --- | --- | --- | --- | --- | --- | --- | --- | --- | --- |
|  |  | Day ‑30^a^to Day 0 |  | 1 | 2 | 3 | | 4 | 5 | 6 | 7 | 8 | 1 | | 12 | 36 | ET |
| Informed Consent | | X* |  |  |  |  |  | |  |  |  |  |  | |  |  |  |
| Determine Eligibility | | X* |  |  |  |  |  | |  |  |  |  |  | |  |  |  |
| Medical History ^b^ | | X |  |  |  |  |  | |  |  |  |  |  | |  |  |  |
| Physical Examination | | X |  |  |  |  | X | |  |  |  | X |  | |  |  | X |
| Review of systems | | X |  |  |  |  |  | |  |  |  |  |  | |  |  |  |
| Height and weight | | X |  |  |  |  |  | |  |  |  |  |  | |  |  |  |
| Vital Signs ^c^ | | X | X |  |  |  | X | |  |  |  | X |  | |  |  | X |
| Concomitant Medications | | X |  | X | X | X | X | | X | X | X |  |  | |  |  | X |
| Adverse Events | |  |  | X | X | X | X | | X | X | X | X | X | | X | X | X |
| PT/INR | | X |  |  |  |  |  | |  |  |  |  |  | |  |  |  |
| CBC with diff/CMP | | X |  |  | X |  |  | |  |  |  | X |  | |  |  | X |
| HCV RNA (Plasma) | | X |  |  | X |  |  | |  |  |  | X |  | | X | X | X |
| Urine β‑hCG ^d^ | |  | X |  |  |  |  | |  |  |  |  |  | |  |  |  |
| Urine Drug Screen | | X* | X | X | X | X | X | | X | X | X | X | X | | X | X | X |
| HCV Genotyping^e^ | | X |  |  |  |  |  | |  |  |  |  |  | |  |  |  |
| HIV Ag/Ab | | X |  |  |  |  |  | |  |  |  | X |  | |  |  | X |
| HBsAg | | X |  |  |  |  |  | |  |  |  |  |  | |  |  |  |
| Stored dried blood spots | |  |  | X | X | X | X | | X | X | X | X |  | | X | X | X |
| Stored samples for SOF and LDV metabolite level | |  |  |  | X |  | X | |  |  |  | X |  | |  |  | X |
| Stored samples for HCV sequence analysis | | X |  |  |  |  |  | |  |  |  | X |  | | X | X | X |
| Randomization to study arm | |  | X |  |  |  |  | |  |  |  |  |  | |  |  |  |
| Motivational-Interviewing based medical adherence counseling | |  | X |  |  |  | X^f^ | |  |  |  |  |  | |  |  |  |
| Motivational-Interviewing based risk reduction counseling | |  | X |  |  |  |  | |  |  |  |  | X | | X |  |  |
| Receive SVR results | |  |  |  |  |  | X | |  |  |  |  | X | |  |  |  |
| Study drug dispensation (unobserved dosing) or directly observed dosing (mDOT) ^f, g^ | |  | X | X | X | X | X | | X | X | X |  |  | |  |  |  |
| Study drug dosing compliance ^h, i^ | |  |  | X | X | X | X | | X | X | X |  |  | |  |  |  |
| Qualitative Interview | |  |  |  |  |  |  | |  |  |  | X |  | |  |  |  |
| ACASI | |  | X |  |  |  | X | |  |  |  | X |  | | X | X |  |
|  | Demographics |  | X |  |  |  |  | |  |  |  |  |  | |  |  |  |
|  | Drug use history |  | X |  |  |  |  | |  |  |  |  |  | |  |  |  |
|  | Injection drug use, injection risk behaviors |  | X |  |  |  | X | |  |  |  | X |  | | X | X |  |
|  | Quality of Life Scale (EQ5-D) |  | X |  |  |  | X | |  |  |  | X |  | | X | X |  |
|  | Depression rating scale |  | X |  |  |  | X | |  |  |  | X |  | | X | X |  |
|  | Severity of dependence scale |  | X |  |  |  | X | |  |  |  | X |  | | X | X |  |
|  | # / HCV status of drug using and injection partners |  | X |  |  |  | X | |  |  |  | X |  | | X | X |  |
|  | Partner-by-partner data on injection/substance use/HCV status |  | X |  |  |  | X | |  |  |  | X |  | | X | X |  |
|  | Participant satisfaction with treatment |  |  |  |  |  |  | |  |  |  | X |  | |  |  |  |

a The screening window can be extended with sponsor approval to 42 days in exceptional circumstances, including the need for additional HCV sequence analysis.

b Should include information regarding (a) the subject’s acquisition of HCV infection and (b) describe any past treatment for their HCV infection.

c Vital signs include resting blood pressure, pulse, respiratory rate and temperature.

d For females of childbearing potential only

e HCV genotype will either be conducted during screening or documentation of prior results will be accepted if they are confirmed to be from the same period of time during which chronic HCV was confirmed with sequential RNA results.

f May move to week 3 depending on when results are received.

g Subjects must be instructed to bring back all bottles of study drug in the original container at every post enrollment study visits through the end of treatment.

h Study drug will be reconciled at every post-enrollment visit by study staff in order to monitor the subject’s adherence with the dosing regimen.

i Enrollment assessments must be performed prior to dosing.

* There are two mandatory screening visits; activities that must be conducted in screening visit one are marked with an *.

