| Statistical Methods: | **Aim 1**: To assess the feasibility of treating active PWIDs for HCV with LDV/SOF by mDOT versus unobserved dosing, as measured by recruitment and retention rates overall and by arm. We will calculate the following feasibility measures: 1) proportion of those eligible among those screened; 2) proportion enrolled among those eligible; and 3) study retention and completion rates, overall and by arm. Process measures (e.g., visit length) and reactions to study procedures will also be assessed. Descriptive statistics will be presented with 95% confidence intervals, to help in interpretation. Between-group differences in retention and completion will be assessed using Fisher’s exact and Wilcoxon tests. We will also calculate Kaplan-Meier curves for time to dropout, by group, and test for differences using the log-rank test.  **Aim 2**: To evaluate the acceptability of mDOT versus unobserved dosing, the percent of treatment medication adherence to LDV/SOF, as measured by the percent of doses taken overall (observed and unobserved), will be assessed using DOT doses and weekend Wise Pill data for the mDOT arm, and WisePill data for the unobserved dosing arm. Other outcomes of interest will include completion of therapy, patterns of adherence, and time to stopping medication. Concordance of the various adherence measures will be examined using weighted Kappa and intraclass correlations. Between-arm differences will be assessed using Fisher’s exact and Wilcoxon tests for outcomes measured once, and GEE models for repeated outcomes. We will also use GEE models to compare WisePill openings and pill counts, accounting for between-arm differences in expected frequency.  Sample size justification: The sample will provide typical precision for a pilot study of feasibility and acceptability outcomes. Specifically, we will be able to estimate the mean of continuous outcomes within margins of sampling error (MSEs; half-widths of 95% confidence intervals) of 0.37 standard deviations (SD) overall, and 0.55 SDs within arm; percentages will be estimated within MSEs of 11-18 points overall, and 15-25 points within arm, depending on the sample value. In designing the full-scale trial, these exploratory results will be cautiously interpreted in the light of confidence intervals, plausibility, and prior results.  **Aim 3**: To assess through in-depth, semi-structured qualitative interviews, the challenges with time intensity required for mDOT versus unobserved dosing, and identify key factors affecting treatment adherence for PWIDs treated with LDV/SOF. Transcribed semi-structured interviews conducted at the End-of-Treatment (week 8 or early termination) visit will be imported into Atlas.ti, a qualitative research software program. We will utilize two qualitative analytic methods to interpret data. First, content analysis will allow us to focus on answering study questions regarding experiences with LDV/SOF treatment and DOT strategies, and opinions on challenges to achieving consistent adherence to treatment. *A priori* themes of interest primarily focused on the time-intensity required for this treatment plan and based upon the team’s experience with HCV treatment among PWIDs will be developed and used as the first codebook with which data are coded. Second, thematic analysis with open coding will allow themes to emerge from the data. A coding system will be developed using an iterative process. In the initial phase, we will review all transcripts and field notes to become familiar with the data, and the analytic team will make notes of their observations and potential codes for use in the initial analysis meeting. Then a codebook, consisting of the code definition and inclusion and exclusion criteria, will be created to aid analysis. In addition to predetermined HCV treatment dimensions, additional codes will be developed independently by each analytic team member through an inductive process of identifying themes that emerge from the data. Group analysis meetings will be held to compare independently developed codes for similarity and further definition. A consensus will be reached regarding each code, its application and definition. To ensure consistency, a codebook and dictionary will be developed with universal definitions for each code.  *Inter-rater reliability*: To ensure reliability and validity in the open-ended component of the in-depth interviews analysis, we will implement a verification strategy to ensure self-correction throughout the analysis process. The two coders will assess inter-rater reliability by calculating the correlation between a set of ratings done by two independent raters for the initial set of 3-6 transcripts, and then again on the next set of 6 transcripts. After each inter-rater reliability assessment, the codebook and codes will be revised based on reconciliation of findings done between coders. Inter-rater reliability will be assessed as a team twice during the analysis process and again at the end of analysis as a post-hoc evaluation of reliability and validity. This evolving analysis process will ensure high quality of research decisions, the rationale behind decisions, and the responsiveness of investigators to the data. Once the codebook is developed and verified all remaining transcripts will be coded. Further meetings will be held to discuss any differences in coding and to ensure consistency in the application of codes.  Final analysis will begin with data reduction, then display, analysis and conclusion drawing using a conceptual framework in which hypothesized factors affecting adherence are assessed and unanticipated findings are identified. The analytic team will work from the coded data to merge findings into a final summary and a consensus of major themes, relationships between themes, and ranking of items of most importance to adherence. This method of data reduction encompassing both site and team based analysis creates a robust iterative process through which the data is thoroughly discussed and analytical consensus achieved. *Atlas.ti* software will be used to both code and develop data displays used in the analysis for this study.  **Exploratory Aims**: While we recognize the small sample size limits our ability to draw firm conclusions from exploratory analyses, the paucity of data for this treatment approach allows for hypothesis-generating results.  *End-of-treatment response and SVR*: We will compare the proportion of participants with undetectable HCV RNA at week 8 and post-treatment week 12 between arms using Fisher’s exact tests.  *Acceptability based on drug levels*: If SVR, retention and/or medication adherence data suggestion medication compliance issues, we may compare SOF metabolite–positivity rates will be calculated by week in both arms; between-group differences will be compared using GEE models for repeated outcomes.  *HCV relapse and reinfection*: Among participants who achieve SVR, we will determine the proportion who experience HCV relapse and reinfection at post-treatment week 36, overall and by arm, with exact 95% confidence intervals. We will sequence HCV RNA in such cases to establish if the event represents relapse versus reinfection.  *Social and injection network analyses to inform a subsequent full TasP trial*: We will characterize injector network sizes at baseline and follow-up. Newman’s method will be used to calculate assortativity coefficients, a measure of the degree of demographic and risk behavior similarity within networks. These findings will help us determine whether a full efficacy trial should use targeted sampling strategies to ensure diversity in network sizes, and whether randomization should be stratified by one or both of these factors in future trials.  **Other Exploratory Outcomes**:  *Drug use behaviors before and after HCV treatment*: Recent data suggest significant changes in drug use behaviors after HCV diagnosis: serosorting with other HCV-positive PWIDs and a sustained reduction in drug use. We will assess these behaviors at baseline and follow-up for preliminary estimates of the possible impact of HCV treatment on these behaviors. ANCOVA and conditional logistic models will be used for continuous and binary outcomes respectively.  *Correlates of Adherence and SVR*: We will explore demographic, behavioral correlates of medication adherence using GEE models for repeated measures. In addition, we will explore demographic and behavioral correlates of SVR using Fisher exact tests and exact logistic regression. |

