## Treatment Discontinuation Criteria

Study drug will be discontinued in the following instances:

- Unacceptable toxicity, as defined in Section 7 of the protocol, or toxicity that, in the judgment of the investigator, compromises the ability to continue study-specific procedures or is considered to not be in the subject’s best interest
- Subject request to discontinue for any reason; it is important to determine whether the withdrawal of consent is primarily due to an AE, lack of efficacy, or other reason
- Discontinuation of the study at the request of Gilead, regulatory agency, or an Institutional Review Board (IRB), with appropriate justification

Study drug *may* be discontinued based on individual case review by both study physicians in the event of pregnancy of a female subject.

If a subject meets discontinuation criteria during treatment, an early termination (ET) visit will be required (Section 6.4). All subjects who meet discontinuation criteria will complete an ET visit, which will include all week 8 procedures, and post-treatment visits at weeks 1, 12 and 36, regardless of the treatment duration.

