## Weekly Treatment Visits (weeks 1-8)

On-treatment study visits (weeks 1, 2, 3, 5, 6, 7) will include directly observed dosing (mDOT) or medication dispensation (unobserved dosing), study drug dosing compliance (pill count), review of concomitant medications and adverse events, urine drug screen, and stored samples for potential testing of SOF and LDV metabolite levels and HCV sequencing, and early termination procedures (if applicable). CBC with diff/CMP and HCV RNA will take place at week 2.

Week 4 visit will include all procedures for weekly study visits as well as symptom-driven physical examination, vital signs, ACASI, HCV RNA, and motivational interviewing for medication adherence.

Week 8 visit will include all procedures for weekly study visits as well as symptom-driven physical examination, vital signs, HCV RNA, CBC with diff/CMP, HCV RNA, HIV Ag/Ab, ACASI, and a qualitative interview.

At each weekly visit, mDOT subjects will receive a 10-trip Muni card to cover weekly round-trip transportation to study site and the unobserved dosing arm will receive a weekly two-trip Muni card to cover round-trip transportation to study site.

Subjects will be compensated $20 for weekly visits 1, 3, 5, 6, and 7; and $25 for the weekly visits with blood draws and/or longer procedures, weeks 2, 4 and 8.

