## Early Termination (ET)

For subjects who terminate early, the ET visit will include the same procedures for a standard week 8 visit. Participants will then be asked to complete post-treatment weeks 1, 12 and 36 starting after last dose of the study drug (post-treatment week 1 visit will be 1 week after ET visit).

Gilead (e.g., Medical Monitor and Clinical Program Manager)/CRO will be informed as soon as possible when a subject discontinues treatment.

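### Appendix 1 contradicts the text and its own footnote h: no qualitative interview at early termination, no pill count at week 8 or early termination, no concomitant medications at week 8, and ACASI at early termination left unsettled

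*Protocol*

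**What the plan says.** **Appendix 1, Study Procedures Table.**
- "Study drug dosing compliance ^h, i": weeks 1 to 7; blank at week 8 and ET.
- "Qualitative Interview": week 8; blank at ET.
- ACASI and its repeated components: enrollment, weeks 4 and 8, post-treatment weeks 12 and 36; blank at ET.
- Concomitant medications: screening, weeks 1 to 7 and ET; blank at week 8.
- Footnote h, attached to the compliance row: "Study drug will be reconciled at every post-enrollment visit by study staff".

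**Text.**
- Section 6.3 lists "study drug dosing compliance (pill count") and concomitant-medication review among the weekly procedures, then states: "Week 8 visit will include all procedures for weekly study visits as well as symptom-driven physical examination". It adds ACASI and the qualitative interview at week 8.
- Section 6.4: "the ET visit will include the same procedures for a standard week 8 visit". Section 3.2 agrees: "All subjects who meet discontinuation criteria will complete an ET visit, which will include all week 8 procedures".
- Section 5.3, in its paragraph on unobserved dosing, has staff counting pills at each visit after enrollment.
- The synopsis (Statistical Methods, Aim 3) describes the interviews as "conducted at the End-of-Treatment (week 8 or early termination) visit".
- Section 6.10 requires the quality of life, depression and dependence scales, all delivered through the ACASI, at ET. The ACASI visit lists in Section 6.7 and the synopsis do not include ET.

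**The concern.** A schedule table is what sites work from. Section 6 presents it as the tabular form of the procedures, and Section 10.1.6 ties case report form content to the protocol's schedule of events and procedures. A form built from Appendix 1 could therefore have no pill-count field at week 8 or ET and no interview at ET.

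The interview matters most. Barriers and facilitators to treatment are a primary endpoint (Section 9.1.2), the interviews serve the third primary objective, and no other instrument is named to replace them. Subjects who stop early are likely to know most about barriers. Omitting them selects the interview sample on the outcome that the interviews are meant to explain.

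The pill count matters less, but it is used: Section 9.5.1 plans GEE models comparing WisePill openings with pill counts. It is also one of the adherence measures available for the planned concordance analysis.

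**Working it through.** **Step 1: are the blanks real?** Each row was read cell by cell against the table header. Physical examination, vital signs and HIV Ag/Ab use the same columns and carry marks at both week 8 and ET. The blanks in the other rows are therefore not a column shift.

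**Step 2: table against text.**

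| Item | Appendix 1 | Text | Result |
|---|---|---|---|
| Qualitative interview at ET | blank | required: 3.2, 6.4, synopsis Aim 3 | contradiction |
| Pill count at week 8 | blank | required: 6.3, 5.3 (unobserved arm), footnote h | contradiction, also within the table |
| Pill count at ET | blank | required: 3.2 and 6.4 through week 8, footnote h | contradiction, also within the table |
| Concomitant medications at week 8 | blank | required: 6.3 | contradiction |
| ACASI at ET | blank | required by 3.2, 6.4 and 6.10; absent from the lists in 6.7 and the synopsis | text itself divided |

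**Step 3: how much is left uncounted?** The protocol gives no figure to reproduce, so this comes from the dispensing schedule.

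- Total doses: 8 weeks × 7 = 56.
- Dispensing is marked at enrollment and weeks 1 to 7, which is 8 occasions. Counts are marked at weeks 1 to 7, so 7 of 8 dispensed weeks are counted. The uncounted one is the week dispensed at week 7: 1/8 = 12.5% of the scheduled counts.
- Unobserved arm (planned n = 10): 7 tablets handed out per week, so 7/56 = 12.5% of doses.
- Modified directly observed arm (planned n = 20): normally two weekend tablets per week go home, so 2/56 = 3.6% of doses. The dosage and administration section allows up to 7 tablets in advance when a visit will be missed, so individual subjects may hold more.

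**Step 4: which endpoints depend on the missing items?**

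- Primary adherence (Section 9.5.1) is the percentage of doses taken. Its sources are observed doses plus weekend WisePill data in one arm and WisePill data in the other. Pill counts are not a source.
- Completion of therapy is nowhere defined by a pill count. Observed-dose and WisePill records remain, as do the study drug start and end dates required by Section 10.1.5.
- Barriers and facilitators rest on the interview.
- ACASI data mainly feed exploratory analyses.

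**Step 5: how many interviews?** The protocol does not say how many subjects are expected to stop early. If k of 30 do and the table is followed, k/30 are missing from the interviews. As an assumption only, k from 0 to 6 gives 0% to 20%.

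**The case against.** The strongest reply is that the text is clear and loss occurs only if staff set it aside. Section 6 says the procedures are also described in the text and supplemented by a manual. Footnote h tells staff to reconcile drug at each visit, so someone who reads the footnotes would still count the last tablets. This lowers the risk for the pill count. It does not help the interview at ET, which has no footnote. In the synopsis its ET timing is stated outright; Section 9.5.1 repeats the interview plan without any timing.

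It can also be said that the week 8 instruction cannot be fully literal, since weekly procedures include dispensing and treatment ends at week 8. That is fair for dispensing, but Section 5.3 and footnote h independently call for the count.

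On ACASI the reply largely stands. The table agrees with Section 6.7 and the synopsis list, so it cannot simply be called wrong.

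A reader might infer that primary adherence and completion data are lost, or that 12.5% of doses go unmeasured in every subject. The documents support neither. Adherence comes from observed doses and WisePill, completion is not tied to a count, and the 12.5% does not carry over to the directly observed arm. Nor can early terminators be assumed to have poor outcomes: Section 3.2 allows stopping for toxicity or at the subject's request, among other reasons.

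**Conclusion.** The contradiction is certain for the interview at ET, the pill count at week 8 and ET, and concomitant medications at week 8. ACASI at ET is an unresolved conflict within the text as well as with the table.

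The main consequence is selection in the interview sample toward subjects who reached week 8, on a primary endpoint. Its size depends on the number of early terminators, which the protocol does not give, and on staff or the case report form having followed the table. The secondary consequence, under the same condition, is a missing last count covering 7 of 56 doses in the unobserved arm and normally 2 of 56 in the directly observed arm. This weakens the WisePill comparison and the final reconciliation, and leaves the primary adherence measure standing. The count may matter more for subjects in facilities that do not permit the WisePill device, an exception the dosing section provides for. The point is worth correcting, but it does not undermine the trial.

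**What to change.** In Appendix 1, mark the qualitative interview at ET, study drug dosing compliance at week 8 and ET, and concomitant medications at week 8. Decide whether ACASI is done at ET and make the synopsis list, Sections 6.7 and 6.10, and Appendix 1 agree; Sections 3.2 and 6.4 need a stated exception if the answer is no. Check the week 8 and ET case report forms against the corrected table.

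Section 4.1 says thirty subjects are already enrolled and one more is planned, so a table correction alone cannot recover anything already missed. The investigator should therefore record, for each early terminator, whether the interview and the final pill count took place, and report the interview status with the qualitative results.

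The cost is a table and wording amendment plus a short check of existing records. Apart from ACASI at ET, which has to be settled, every procedure concerned is already required by the text.
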